# Therapeutic effects and central mechanism of acupuncture and moxibustion for treating functional dyspepsia: study protocol for an fMRI-based randomized controlled trial

**DOI:** 10.1186/s13063-022-06411-9

**Published:** 2022-06-06

**Keywords:** Functional dyspepsia, Central mechanism, Acupuncture, Moxibustion, Functional magnetic resonance imaging

## Abstract

**Background:**

Functional dyspepsia (FD) is one of the most common functional gastrointestinal disorders, with a high prevalence and significant influence on the quality of life (QoL). Either acupuncture or moxibustion is effective for dyspepsia, which is confirmed by both ancient documents and modern research. However, the therapeutic advantage and underlying mechanism between acupuncture and moxibustion for FD remain unclear.

**Methods:**

This randomized controlled fMRI trial aims to (i) evaluate the therapeutic advantages of acupuncture and moxibustion treatment for FD, (ii) investigate the similarities and differences in cerebral activity elicited by acupuncture and moxibustion, and (iii) analyze the possible correlations between brain responses and clinical variables thus to explore the potential central mechanism of acupuncture and moxibustion for treating FD. Ninety-two FD patients will be randomly assigned to either the acupuncture group or the moxibustion group in a 1:1 ratio. Twenty sessions of acupuncture or moxibustion treatment over 4 weeks will be performed on each patient. The short form Leeds Dyspepsia Questionnaire, the Nepean Dyspepsia Index, etc., are used to evaluate the therapeutic effects. The heart rate variability will be analyzed to investigate the autonomic nerve function. Thirty-six FD patients in each group will be randomly selected for the fMRI scan to detect cerebral activity changes.

**Discussion:**

We expect the results will deepen our knowledge on the clinical value and underlying mechanism of acupuncture and moxibustion and provide a reference for a better selection of interventions for treating FD.

**Trial registration:**

Chinese Clinical Trial Registry (www.chictr.org.cn) ChiCTR2100049496. Registered on 2 August 2021

**Supplementary Information:**

The online version contains supplementary material available at 10.1186/s13063-022-06411-9.

## Background

Functional dyspepsia (FD), as one of the common functional gastrointestinal disorders (FGIDs), refers to a group of upper gastrointestinal syndromes, including epigastric pain, epigastric burning, meal-related fullness, and early satiation [1]. According to the Roma IV criteria, FD can be divided into three subgroups, the postprandial distress syndrome (PDS), the epigastric pain syndrome (EPS), and the overlap [2]. It was estimated that 80% of patients with dyspepsia are diagnosed as FD; what is worse, FD affects up to 16% of the individuals in the general population [3, 4]. Although FD is not a lethal disease, it significantly reduces patients’ quality of life (QoL) and impose an enormous socioeconomic burden on the healthcare financial system [5]. In the USA, the medical expense was estimated to be over $18 billion per year [6].

Acupuncture and moxibustion have been used for gastrointestinal symptoms for more than 2500 years in China and are increasingly accepted as the nonpharmacologic alternative therapies for FGIDs around the world [7–9]. Recent clinical studies have demonstrated that both acupuncture and moxibustion could effectively relieve symptoms and improve the QoL of FD patients [10, 11]. However, the advantages and the underlying mechanisms of acupuncture and moxibustion in the treatment of FD have not yet been fully elucidated.

In Roma IV criteria, FD is defined as a disorder of brain-gut interaction [12]. Therefore, exploring the pathological characteristics and therapeutic effect targets of FD from the perspective of brain activity arouses increasing attention in the past two decades. By neuroimaging techniques including PET and MRI, people found that FD patients have significant cerebral functional abnormalities and structural alterations, and the cerebral changes are related to their symptoms [13–17]. For example, our previous studies indicated that the anterior cingulate cortex (ACC), insula, thalamus, middle cingulate cortex (MCC), and cerebellum might be the key regions that were close to the severity of dyspepsia symptoms [18, 19]. Furthermore, studies have suggested that acupuncture treatment can effectively modulate the abnormal cerebral activities to improve dyspepsia symptoms and QoL, and moxibustion treatment also can elicit the cerebral signal changes in FGIDs patients [19–22]. These studies provide the possibility to explore the different therapeutic mechanisms between acupuncture and moxibustion from the central responses. Based on our previous studies, the present study is conducted to (i) evaluate the therapeutic advantages of acupuncture and moxibustion treatment for FD, (ii) investigate the similarities and differences in cerebral activity elicited by acupuncture and moxibustion, and (iii) analyze the possible correlations between the brain responses and clinical variables thus to explore the potential central mechanism of acupuncture and moxibustion respectively.

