## Methods/design

### Design and setting

The present study is a single-center, parallel-controlled, equivalence, randomized clinical trial, and a total of ninety-two patients with FD will be recruited. These patients will be randomly allocated into either the acupuncture group or the moxibustion group with a 1:1 ratio. The study period includes a 1-week baseline, 4 weeks of treatment, and another 4 weeks of follow-up. Clinical measurements will be performed at the baseline, at the end of the treatment, and at the end of follow-up, respectively. Neuroimaging scans will be performed at the baseline and the end of the treatment. More details of the study design are shown in Fig. 1 and Table 1.

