### Blinding

It is difficult to blind acupuncturists and patients in this trial for different types of intervention. Acupuncturists will not participate in any outcome assessment process. All the outcome assessors and statisticians will be masked in randomization assignments and intervention during the whole study.

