### Sample size calculation

The sample size was estimated based on the results of a study on the changes in the short form Leeds Dyspepsia Questionnaire (SF-LDQ) in response to a 4-week acupuncture intervention versus moxibustion intervention, which showed a mean improvement of the SF-LDQ was − 5.62 ± 2.81 (mean ± SD) in the acupuncture group and − 3.56 ± 2.62 in the moxibustion group respectively [25]. It provides an effect size (Cohen's *d* = 0.758) to estimate the sample size of this study. To achieve 90% statistical power (*α* = 0.05), at least 76 participants are needed. Besides, assuming a 20% attrition rate, ninety-two participants (46 participants per group) will be recruited to detect a two-sided significant difference. The sample size calculation steps are shown in Supplementary file 4.

According to previous fMRI-based studies [26, 27], thirty subjects or more can notably improve the reliability of results. Considering the dropout rate or loss of data due to head motion during fMRI scanning, in this study, thirty-six participants in each group will be randomized to fMRI scans.

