#### fMRI data analysis

The fMRI data will be analyzed with MATLAB 2 017b (MathWorks Inc., Natick, MA, USA). After data preprocessing, amplitude of low-frequency fluctuation (ALFF), functional connectivity (FC), and large-scale functional brain network analysis, etc. will be conducted to investigate the difference of central responses between acupuncture and moxibustion. In voxel-based analysis, the threshold will be set to *p*<0.01 in voxel-level and *p*<0.05 with false discovery rate in cluster-level. While in connectome-based analysis, the threshold will be set to *p*<0.05 with false discovery rate corrected. Furthermore, the Pearson correlation analysis between the clinical results and fMRI results will be conducted to investigate the potential correlation between symptom improvements and brain activity changes elicited by different interventions.

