To explore the similarities and differences in potential mechanism, the MRI  scans will be performed on the selsected patients in each group, and the HRV tests will be performed on all the patients, at the baseline and the end of the treatment. Using 24-h dynamic ECG, the HRV changes of FD patients in each group will be calculated to investigate the influence of acupuncture and moxibustion on the function of the autonomic nerve. By MRI scan, the cerebral activity changes will be analyzed to explore the brain responses to acupuncture and moxibustion, respectively. In addition, by correlation analysis, the correlations among HRV changes, cerebral activity alteration, and clinical variables improvement in each group will be used to further explore the characteristics in the pattern of central responses to acupuncture or moxibustion.

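### With two active arms and no concurrent comparison, imaging or HRV change common to both arms cannot be attributed to treatment, so the similarities half of aim (ii) needs rewording

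*Protocol article*

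**What the plan says.** The Background (and the Abstract, under Methods) sets aim (ii): "investigate the similarities and differences in cerebral activity elicited by acupuncture and moxibustion". The Discussion section on similarities and differences between the treatments restates it as a question of mechanism, "To explore the similarities and differences in potential mechanism", and says how the scans will be read: "the cerebral activity changes will be analyzed to explore the brain responses to acupuncture and moxibustion, respectively". The same paragraph treats the HRV change in each group as showing the influence of the two treatments on autonomic function.

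On design, Design and setting gives two arms: "These patients will be randomly allocated into either the acupuncture group or the moxibustion group with a 1:1 ratio". It fixes the scan times: "Neuroimaging scans will be performed at the baseline and the end of the treatment". Sample size calculation adds that "thirty-six participants in each group will be randomized to fMRI scans". The fMRI rows of Table 1 list the same two groups and nobody else. Blinding concedes that "It is difficult to blind acupuncturists and patients in this trial for different types of intervention". Concomitant treatments lets patients with unbearable symptoms take drugs, which are recorded.

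The only group contrast named under fMRI data analysis is between arms: the imaging analyses "will be conducted to investigate the difference of central responses between acupuncture and moxibustion".

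**The concern.** The aim is phrased causally for similarities as well as differences. The differences half rests on a randomised contrast. The similarities half can rest only on pre-to-post change within each arm, and nothing in the design separates that change from what the same patients would have shown without either treatment. The Discussion nonetheless reads each arm's imaging and HRV change as the response to, or influence of, that arm's treatment.

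At stake is what the trial may conclude about mechanism. If a region or an HRV index moves in the same direction in both arms, the plan's wording leads to reporting it as something both treatments produced. The data would fit equally well with neither treatment having produced it. The article states no such limitation.

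**Working it through.** **Identification.** Let A and M be the true effects of acupuncture and moxibustion on some imaging or HRV measure, and S the change that would occur anyway over the period.

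- Expected change, acupuncture arm: A + S
- Expected change, moxibustion arm: M + S
- Difference between arms: A − M

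There are two observable means and three unknowns. S cancels from the difference, so A − M is identified. A shared change of size x arises from A = M = x with S = 0, and equally from A = M = 0 with S = x. No analysis of these two arms alone can tell the two cases apart.

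**What may enter S, from the document.** Time and natural course of a symptomatic condition (Inclusion criteria); expectation, since patients are not blinded (Blinding); drugs taken during the trial (Concomitant treatments); repeat scanning (Design and setting). The document gives no size for any of these.

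**Illustration.** The plan gives no figure on this point to reproduce, so the size can only be illustrated.

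Inputs:
- Pairs per arm: 30. Sample size calculation cites thirty or more as the target and sets 36 to allow for losses.
- Thresholds: p<0.05 two-tailed (Clinical data analysis) and the voxel-level p<0.01 (fMRI data analysis).
- Retest correlation r = 0.5 to 0.7: assumption.
- Entry offset k = 0.3, 0.5 or 1 SD from the long-run mean on the tested measure: assumption.
- Treatment effect: zero in both arms.

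Formulas:
- Drift = k(1 − r) SD.
- SD of change = √(2(1 − r)).
- Standardised change dz = k√((1 − r)/2).
- One arm significant in the direction of the drift: upper tail of the noncentral t with 29 df and noncentrality dz√30, beyond 2.045 (p<0.05) or 2.756 (p<0.01).
- Both arms: the square of that.

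Example, k = 1 and r = 0.5: drift 0.5, SD of change 1.0, dz 0.50, noncentrality 2.74; one arm 75.4%, both arms 0.754² = 56.8%. With r = 0.7: drift 0.3, SD 0.775, dz 0.387; one arm 53.6%, both 28.8%.

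| Entry offset | dz (r = 0.7 to 0.5) | One arm, p<0.05 | Both arms, p<0.05 | Both arms, p<0.01 |
|---|---|---|---|---|
| 0.3 SD | 0.12 to 0.15 | 9-12% | 1-2% | about 0.1% |
| 0.5 SD | 0.19 to 0.25 | 18-26% | 3-7% | 0.3-1% |
| 1 SD | 0.39 to 0.50 | 54-75% | 29-57% | 8-25% |

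The p<0.01 column is for a single test before cluster correction, which would lower the rates further. In every row the between-arm test keeps its nominal error rate, because S cancels. More patients do not help: at dz = 0.50 and p<0.05, going from 30 to 36 pairs per arm raises the both-arms rate from 57% to 69%.

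**The case against.** A head-to-head trial without a sham arm is a legitimate design, and the fMRI analysis section already names the between-arm contrast. The imaging aim is exploratory and not primary, and the labelling of within-arm results could be left to a fuller plan. All of this stands, and it limits the point to one of wording. It does not remove it: the causal phrasing of the aim and the reading of each arm's change are fixed in this article, and a later analysis plan cannot supply a missing comparator. The earlier imaging studies cited in the Background are not concurrent controls for these patients.

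A reader might infer three stronger things that the documents do not support.

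- **That a spurious shared change is likely, at the 29-57% level.** That figure needs patients to enter a full 1 SD off on the brain measure itself. They are selected on a Rome IV diagnosis, not on imaging or HRV values, so regression to the mean reaches those measures only as far as they track the diagnosis. Smaller offsets, or the protocol's own voxel threshold, bring the rate down sharply.
- **That the plan announces a common central mechanism.** It uses no such phrase and describes no conjunction or similarity test. Its wording is about exploring potential mechanisms.
- **That within-arm symptom change will be presented as efficacy.** Aim (i) is comparative, and the article announces no such within-arm test.

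**Conclusion.** The point holds as a limit on attribution. The design supports inference about the difference between acupuncture and moxibustion in imaging and HRV change. It does not support the similarities half of aim (ii) as worded, or the Discussion's reading of each arm's change as that treatment's effect. This follows from the two-arm structure and needs no numerical assumption.

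The practical size is uncertain. Across the assumed offsets and retest correlations, a false shared change runs from about 1% to 57% of trials at p<0.05, and from about 0.1% to 25% at p<0.01 before cluster correction. The documents do not say where in that range the trial lies, and expectation, time and repeat scanning could add drift of unknown size.

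The severity is minor. The primary SF-LDQ result is a between-arm comparison and is untouched, and no third arm is needed for the question the randomisation answers.

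**What to change.** Reword aim (ii) in the Abstract and Background, and the matching paragraph of the Discussion, as follows.

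1. The inferential imaging and HRV result is the between-arm difference at end of treatment, adjusted for baseline. This agrees with the contrast already named under fMRI data analysis.
2. Within-arm changes, and changes common to both arms, are reported as descriptive changes over the treatment period. They are not described as produced by, or as a mechanism of, either treatment.
3. A limitation states that, without a concurrent sham or untreated comparison, shared change cannot be separated from time, natural course, expectation, concomitant drugs and repeat scanning.

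This needs no new patients, scans or arms. The cost is a more modest claim about shared mechanism.

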## Methods/design

### Design and setting

The present study is a single-center, parallel-controlled, equivalence, randomized clinical trial, and a total of ninety-two patients with FD will be recruited. These patients will be randomly allocated into either the acupuncture group or the moxibustion group with a 1:1 ratio. The study period includes a 1-week baseline, 4 weeks of treatment, and another 4 weeks of follow-up. Clinical measurements will be performed at the baseline, at the end of the treatment, and at the end of follow-up, respectively. Neuroimaging scans will be performed at the baseline and the end of the treatment. More details of the study design are shown in Fig. 1 and Table 1.

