#### Primary outcome measurements

Our primary outcome is the improvement of SF-LDQ after 4 weeks of treatment. The SF-LDQ is a validated and reliable tool to measure the frequency and severity of five dyspeptic symptoms (epigastric pain, postprandial fullness, indigestion, epigastric burning, and postprandial nausea) [32]. Graded on a 5-point Likert scale, the higher the score of the five symptoms, the more severe the disorder.

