### Data analysis

#### Clinical data analysis

All analyses will be done on the ITT population. An independent statistician will conduct clinical data analysis with SPSS 24.0 software (SPSS Inc., Chicago, IL, USA). Kolmogorov–Smirnov test will be used to analyze data distribution, and Levene’s test will be used to analyze homogeneity of variance. The quantitative variables will be presented as mean and SD or median and interquartile, whereas qualitative measures will be reported as percentages with 95% CI. Analysis of variance (ANOVA) test will be used with Bonferroni post hoc comparisons for continuous variables. The independent-samples *t*-test or the Mann-Whitney *U* test for continuous variables and the chi-square test, Fisher exact test, or Kruskal–Wallis test for categorical variables will be used, when suitable. We will describe 24-h HRV using time-domain measurements. Time-domain indices of HRV quantify the amount of variability in measurements of the interbeat interval (IBI), which is the time period between successive heartbeats. These values may be expressed in original units or as the natural logarithm (Ln) of original units to achieve a more normal distribution [41]. Pearson's coefficient will be used for bivariate correlations. All the statistical significance threshold tests will be set to *p*<0.05 with a two-tailed test.

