## Discussion

This randomized control fMRI trial will compare the differences in clinical effects and the central responses between acupuncture and moxibustion. The results might deepen our understanding of the advantages and central mechanisms of acupuncture and moxibustion for FD and besides provide a reference for a better selection of interventions for treating FD.

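### The protocol labels the trial an equivalence trial, but sizes and tests it for a two-sided difference and states no equivalence margin

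*Protocol article*

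**What the plan says.** Four parts of the protocol article bear on the primary hypothesis.

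- **Design and setting** gives the framework: "The present study is a single-center, parallel-controlled, equivalence, randomized clinical trial".
- **Sample size calculation** takes the planning values from a previous study: an improvement of "5.62 ± 2.81 (mean ± SD) in the acupuncture group" against "3.56 ± 2.62 in the moxibustion group". This gives d = 0.758, and 76 evaluable patients for 90% power at α = 0.05. It then says that "ninety-two participants (46 participants per group) will be recruited to detect a two-sided significant difference".
- **Clinical data analysis** names the independent-samples t-test or Mann-Whitney test (with ANOVA and post hoc comparisons) on the ITT population. On the decision rule it says "All the statistical significance threshold tests will be set to" p<0.05, two-tailed.
- **Aims and Discussion** describe a difference question. The Background aims to "evaluate the therapeutic advantages of acupuncture and moxibustion treatment for FD", and the Discussion says that the trial "will compare the differences in clinical effects and the central responses between acupuncture and moxibustion".

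The primary endpoint is clear: "Our primary outcome is the improvement of SF-LDQ after 4 weeks of treatment". The article gives no equivalence margin, no two one-sided tests and no rule that compares a confidence interval with a margin. It does not say how a non-significant result would be interpreted.

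**The concern.** An equivalence trial and a difference trial have opposite hypotheses. In the first, the alternative is that the arms differ by less than a stated margin. In the second, it is that they differ at all. The design section commits to the first. The sample size and analysis sections carry out the second, and the planning assumption is that the arms differ by 2.06 points.

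The label governs what may be concluded from the primary SF-LDQ result. If it stands, the planned tests give no valid route to an equivalence conclusion, and the stated 90% power says nothing about the chance of reaching one. With the framework left ambiguous, either a significant or a null result could be presented as fitting the design. The trial is meant to inform the choice between two treatments, so its primary hypothesis should be settled before results are known.

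**Working it through.** **Inputs (Sample size calculation).** Mean improvements 5.62 and 3.56 points; SDs 2.81 and 2.62; α = 0.05; power 90%; 76 evaluable; 20% attrition; 46 recruited per arm.

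**1. Reproduce the plan's figure.**
- Difference: 5.62 − 3.56 = 2.06.
- Pooled SD: √((2.81² + 2.62²)/2) = 2.717.
- d = 2.06/2.717 = 0.758, as stated.
- Two-sided two-sample t-test, noncentrality d·√(n/2). With n = 37 per arm, power is 0.896; with n = 38, 0.904. So 38 per arm, 76 in total, matches exactly.
- The one-sided normal formula gives 30 per arm (60), which does not match.

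The 76 is therefore a two-sided difference calculation and needs no margin to explain it.

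**2. Sample sizes used below.** 46 per arm is everyone recruited. After 20% attrition, 46 × 0.8 = 36.8, taken as 37 per arm.

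**3. Precision.** The half-width of the 95% CI is t × 2.717 × √(2/n):
- 46 per arm: 1.987 × 0.566 = 1.13 points.
- 37 per arm: 1.993 × 0.632 = 1.26 points.

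**4. Chance of a non-significant two-sided test** (noncentral t). The 1.0-point difference is my assumption; 2.06 is the plan's own value.

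| True difference | 46 per arm | 37 per arm |
|---|---|---|
| 1.0 | 58% | 65% |
| 2.06 | 5% | 10% |

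**5. Equivalence power.** Two one-sided t-tests (TOST) at 5% each, true difference zero, SD 2.717, averaged over the distribution of the sample SD. The article gives no margin, so these margins are assumptions shown as a range.

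| Margin (points) | 46 per arm | 37 per arm |
|---|---|---|
| 1.0 | 10% | 2% |
| 1.5 | 67% | 52% |
| 2.0 | 94% | 86% |

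With the planned 38 evaluable per arm, equivalence power reaches 90% only at a margin of about 2.07 points. That is as wide as the 2.06-point difference that the plan sets out to detect. If the planned 2.06 points is the true difference, TOST would declare equivalence with probability at most 5% for any margin up to 2.06.

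**The case against.** The best defence is that the word is a slip. It appears once, as an adjective in the design sentence. Everything operational (the clinical aim, the effect size, the sidedness, the tests and the Discussion) describes a difference trial. On that reading the sizing, its 90% power and the primary comparison are coherent. This largely stands. It explains the error and points to the cheaper correction, but the framework is still misstated.

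A reader might infer that p>0.05 would be read as equivalence, or would count as success. The article says neither, and its aims point the other way. The point is conditional: if the label stands and p>0.05 were read as equivalence, that reading would have no error control. At the planned 2.06 points a non-significant result is in any case uncommon.

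The equivalence power depends heavily on the margin. At 2.0 points it is respectable, and the article gives no basis for preferring any margin.

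A reader might also object to ITT as the only analysis set. That matters only if equivalence is the real objective, and supporting sets are commonly left to an analysis plan.

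Supplementary file 4, with the sample size steps, is not shown. A margin there would still contradict the sample size section, and the 76 is fully explained without one.

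**Conclusion.** The contradiction is real and lies in the text itself: an equivalence label set against difference sizing and difference tests. It is not an omission that an analysis plan could fill, because the article states both the framework and a conflicting sizing goal.

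The label is the likely error. The 90% power belongs to a two-sided difference test and does not carry over to equivalence at any margin narrower than the planned effect. The documents do not show that the primary comparison is invalid, or that a null result will be claimed as equivalence.

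The sizes rest on the plan's SDs and a normally distributed outcome. The 1.0-point true difference, the three margins and the zero true difference in the equivalence calculation are my assumptions. The reproduction of 76 needs none of these three.

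**What to change.** In Design and setting, replace equivalence with superiority (two-sided test of a difference). In Clinical data analysis, state that the primary result is the between-arm difference in SF-LDQ improvement with its 95% CI, and that a non-significant p-value will not be reported as equivalence or similar efficacy. This costs a few words and a sentence or two, needs no extra patients on this account, and leaves the 76-evaluable sizing and its power as they are.

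Only if equivalence is truly intended: pre-specify and justify a margin, use TOST (confidence interval judged against the margin) with a supporting per-protocol analysis, and replace the 90% power statement with the equivalence power that the sample delivers. That route may cost patients. For 90% power at one-sided 5% and a true difference of zero, an assumed margin of 1.5 points needs 72 evaluable per arm, and a margin of 2.0 needs 41, against the planned 38.
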